## Methods

### Study Design

The study is designed as a randomized controlled trial (RCT). The RCT will include an experimental group, in which participants will undertake the psychosocial intervention, and a control group, where participants will receive support according to the traditional self-help methodology. Interventions for both groups will last 4 months and will be comprised of 16 sessions. The following evaluation phases are planned: T0 (baseline), T1 (end of treatment), and T2 (follow-up at 6 months). At each stage, a self-assessment questionnaire will be administered as described in Multimedia Appendix 1. Figure 1 describes the experimental design.

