### Participants, Recruitment, and Sample Size

The sample consists of family caregivers of people with Alzheimer disease who are followed by the Alzheimer Center of the Istituto di Ricovero e Cura a Carattere Scientifico (IRCCS) Istituto Nazionale di Ricovero e Cura per Anziani (INRCA) of Ancona. No limits are set for the ages of both the patient and the caregiver, nor for the type of family relationship between them.

Eligibility criteria for caregivers include the following:

Signed an informed consent formAged 18 years or olderIs a caregiver for a person with mild to moderate Alzheimer diseaseThe person with Alzheimer disease resides at their home or at the patient’s own home.

Exclusion criteria include the following:

The caregiver failed to meet the inclusion criteriaThe family member with Alzheimer disease has psychiatric disorders that were detected before the diagnosis of Alzheimer diseaseThe family members of the patient with Alzheimer disease have psychiatric disorders that were detected before the diagnosis of Alzheimer disease.

The type of intervention hypothesized for this study and the expected efficacy for the case group is comparable to the work of Küçükgüçlü et al [15]. The authors of this work, which included 30 individuals, obtained an average reduction in caregiver burden of 4.61 points, corresponding to an effect size of 0.243.

Assuming the same effect size in our group of cases, setting the statistical power at 90% and a significance level of .05, it was estimated through repeated-measures within-factors analysis of variance (ANOVA)—two groups and two measurement times (ie, baseline and follow-up)—that the total sample size expected must be at least 48 subjects. Considering a dropout rate of about 20%, the sample size increased to 58 subjects: 29 cases and 29 controls.

Recruitment was carried out during daily visits to the Alzheimer Centre of the IRRCS INRCA in Ancona, where the older person was accompanied by a family member. Once the criteria for participation were established and met, a proposal to join a support group was made, the caregiver chose whether or not to participate, and the caregiver was randomly placed in one of the two groups.

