
Regarding the control group, the minimum number of participants will be 3 and the maximum number will be 12. This group includes 16 meetings: 1 for the presentation of the study to the participants and for the administration of the questionnaire, 14 for free discussions, and 1 final meeting for the administration of the questionnaire and conclusion of the group intervention. The control group will follow self-help methodology in such a way that the facilitator will have the sole task of facilitating communication between members of the group as the topics are chosen and treated freely by participants.

For both groups, each session will last 1.5 hours. During the first meeting for both groups, the informed consent forms with explanations about the intervention will be completed and the first questionnaires will be completed. In the final meeting, participants from both groups will complete the final questionnaire; after 6 months, they will be contacted by the researchers for the follow-up assessment.

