### Data Analysis

A descriptive analysis of the sample will be carried out through univariate and bivariate statistical analysis. Continuous variables will reported as mean and SD or median and IQR, based on their distribution, and will be evaluated using the Shapiro-Wilk test. The comparison of variables between groups at baseline will be carried out by means of unpaired Student *t* tests or Mann-Whitney *U* tests, based on their distribution. Categorical variables will be expressed as absolute frequencies and percentages, and statistical significance will be evaluated using chi-square tests or Fisher exact tests, in the case of comparisons between small subsamples.

In the second phase, the analysis of follow-up data will be carried out in order to assess the effectiveness of the intervention. This phase of analysis involves the use of multivariate statistical techniques, in particular, repeated-measures ANOVA, in order to compare changes in outcome measures over time between the intervention group and the control group. In the case of different exposure times between subjects, the Cox regression model will be employed in order to identify factors associated with the change in key endpoints. Statistical significance will be set at *P*<.05.

Every effort will be made to collect all data within the specified time frame. In the case of missing and unrecoverable data on the primary endpoints, we will assume that these events are related to chance. Analyses will be performed by applying list-wise deletion to remove cases with missing values from the final database in order to obtain unbiased estimates.

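### List-wise deletion is credited with giving unbiased estimates, but it only inherits an unjustified chance assumption and, as worded, discards observed T1 scores

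*Protocol article*

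**What the plan says.** All references are to the protocol article.

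- **Data Analysis, missing data.** The assumption comes first: "In the case of missing and unrecoverable data on the primary endpoints, we will assume that these events are related to chance". The rule follows: "Analyses will be performed by applying list-wise deletion to remove cases with missing values from the final database in order to obtain unbiased estimates".
- **Data Analysis, method.** Effectiveness is assessed with "repeated-measures ANOVA, in order to compare changes in outcome measures over time between the intervention group and the control group". The target is therefore a difference in change, not in level.
- **Study Design.** There are three assessments: baseline (T0), end of treatment (T1) and a 6-month follow-up (T2).
- **Intervention.** T1 is tied to attendance: "In the final meeting, participants from both groups will complete the final questionnaire". For T2, researchers contact participants.
- **Participants, Recruitment, and Sample Size.** The calculation uses two measurement times, gives 48, and is raised to 58 for about 20% dropout.
- **Randomization.** Participants who leave are not replaced.

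**The concern.** The rule reverses the logic. Removing incomplete cases cannot make an estimate unbiased. The estimate is unbiased only if the retained cases are, for the contrast of interest, like those removed. The article declares that condition but does not argue for it.

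There are reasons to doubt it here. The outcome is caregiver burden, itself a plausible reason to stop attending. The arms differ in format (facilitator-led topics against free discussion), so reasons for leaving may differ too. A caregiver who stops attending misses T1 by the route described. The Discussion itself expects that restrictions in the COVID-19 period may affect participation.

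The wording also removes cases from the final database. Applied across three waves, that drops a caregiver with complete T0 and T1 because T2 is absent. The result is then a comparison of completers, not of the groups as randomised. The bias can go either way. If the more burdened leave the control arm, the benefit is understated; if they leave the experimental arm, it is overstated.

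**Working it through.** **1. The plan's own figures.** Take 0.243 as Cohen's f, two measurement times, alpha 0.05, and an assumed within-person correlation rho = 0.5 (not stated in the article).

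- Noncentrality = f² × N × 2 / (1 − rho) = 0.243² × 48 × 2 / 0.5 = 11.34, with 1 and 46 degrees of freedom. Power is 0.909.
- At N = 46 power is 0.897, so 48 is the smallest even N that reaches 90%. The stated 48 reproduces.
- 48 × 1.2 = 57.6, which gives the stated 58. A 20% loss leaves 58 × 0.8 = 46.4, about 46 complete cases, with power about 0.897.

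The sample size is therefore not the problem.

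**2. A yardstick for bias.** Read as the f of a two-level factor, 0.243 corresponds to 2 × 0.243 = 0.486 SD, about 0.49 SD. This is an assumption used for scale; the article does not say which contrast its effect size describes.

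**3. Dropout driven by T1 burden in one arm, T1 unobserved in those who leave.** The assumed model is logit P(dropout) = a + b × (T1 burden in SD units), with a set to give 20% missing. The other arm's dropout is unrelated to burden. SDs are equal at T0 and T1.

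- b = 0.5 (odds × 1.65 per SD, a = −1.459): the completers' mean T1 level shifts by −0.096 SD.
- b = 1.0 (odds × 2.7 per SD, a = −1.650): it shifts by −0.173 SD.

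The completers' T0 mean shifts by rho times as much, so the shift in change is (1 − rho) × the level shift:

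| rho | b = 0.5 | b = 1.0 |
|---|---|---|
| 0.3 | −0.067 | −0.121 |
| 0.5 | −0.048 | −0.087 |
| 0.7 | −0.029 | −0.052 |

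At rho = 0.5: 0.048 / 0.486 = 10% and 0.087 / 0.486 = 18%.

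**4. T1 observed in everyone, about 20% missing at T2.** This was simulated with 2 million participants, correlation 0.7 between adjacent waves (0.49 between T0 and T2), and a true effect of −0.486 SD at T1 and T2. The T1 change contrast after list-wise deletion was:

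| What T2 dropout depends on | T1 contrast |
|---|---|
| Chance | −0.487 |
| Arm only | −0.486 |
| Baseline burden only | −0.485 |
| T1 burden, same rule in both arms | −0.471 |
| T1 burden, control arm only | −0.431 |
| T1 burden, opposite directions by arm | −0.379 |

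The last two are attenuated by 0.055 / 0.486 = 11% and 0.107 / 0.486 = 22%. Keeping the observed T1 scores returns about −0.486. The T2 contrast stayed near −0.486 throughout, because under these correlations the T0-to-T2 change is uncorrelated with T1.

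**5. What the mixed model does in the step 3 case.** At rho = 0.5 a likelihood analysis that keeps all T0 values is biased by about −0.072 SD (b = 0.5) and −0.133 SD (b = 1.0), against −0.048 and −0.087 for list-wise change. It does not cure dropout driven by unobserved T1 burden.

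**The case against.** The best defence is that the article states its assumption openly, promises every effort to collect the data, and limits the rule to unrecoverable values. If missingness really is by chance, deletion is unbiased, as the first row of step 4 shows. This is fair: the article is not silent, and non-attenders at meeting sixteen may be pursued. It still does not make deletion the source of unbiasedness.

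Second, the sample size uses two times. If the primary ANOVA used only T0 and T1, caregivers without T2 could stay in. That is possible, but the deletion rule is not limited to two waves. The loss of T1 data is therefore conditional on an analysis of all three waves or on deletion across the whole database as worded.

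Third, step 5 shows that the proposed model is no remedy for dropout driven by unobserved burden, and in that case it is worse than list-wise change. This stands. The case for the model is that it keeps every observed score, is valid under the plan's own chance assumption, and stays valid under the weaker missing-at-random assumption.

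Three stronger readings are tempting but unsupported:

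- A reader might infer that any dropout related to arm or burden causes bias. Dropout related to arm alone, or to baseline burden alone with a constant effect, left the change contrast unbiased.
- A reader might set the level shifts of 0.096 to 0.173 SD against an effect of 0.24 to 0.49 SD and infer a bias of 20 to 70% of the target. The plan compares changes, and its 48 reproduces with 0.243 as f.
- A reader might treat T1 and T2 as independent 20% losses and infer 0.8 × 0.8 × 58, about 37 complete cases. The article's figure is about 20% dropout overall, which leaves about 46.

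**Conclusion.** The point holds in a limited form. The sentence is wrong as written: deletion relies on the chance assumption and does not deliver unbiasedness, and the article does not justify that assumption. The threat to the planned contrast is dropout related to post-baseline burden, above all when it differs by arm.

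In the one-arm illustration, the bias in the T1 change contrast is about 0.05 to 0.09 SD at correlation 0.5, and 0.03 to 0.12 SD over correlations from 0.7 to 0.3. At correlation 0.5 that is roughly 10 to 18% of a 0.49 SD target. Where T1 was observed and only T2 is missing, keeping the T1 scores removes this bias. All these sizes rest on assumed dropout models, correlations and equal SDs, because the article gives none. They show what could happen, not that it will.

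**What to change.** - Delete the list-wise rule and the claim that it yields unbiased estimates.
- Analyse all randomised participants in their assigned arm with a likelihood-based mixed model that uses every observed T0, T1 and T2 score. State that it is valid under missing at random.
- Report dropout by arm.
- Because this model does not correct dropout driven by unobserved burden, add one delta-adjusted sensitivity analysis for the Caregiver Burden Inventory.

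The cost is a change of wording and a little more analysis work, with no new participants or visits. Extra T1 contacts are not proposed for groups whose T1 has passed: enrolment ran to September 2022, so for those groups only the analysis can still be changed.

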### Ethics Approval

The study was approved by the Ethics Committee of the IRCCS INRCA on November 26, 2020 (approval No. CE INRCA 20018). The Ethics Committee will be notified about any protocol modifications. The Ethics Committee is in charge of data monitoring and will periodically assess the progress of the protocol and compliance with what was declared. The study will adhere to the principles of the Declaration of Helsinki and Good Clinical Practice guidelines. Participants in this study will provide written informed consent.

## Results

Participant recruitment, enrollment, and data collection began in 2021. Enrollment continued until September 2022, at which time the last group began the intervention. Data collection will be completed by December 2022, and data analysis will be completed by March 2023. The study findings will be published in peer-reviewed scientific journals and will be presented at scientific meetings. Summaries of the results will also be made available to investigators for dissemination within their clinics.

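### The December 2022 end of data collection comes before the last group's 6-month follow-up on any reading of the schedule

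*Protocol article*

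**What the plan says.** All statements are in the protocol article.

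- **Calendar (Results, repeated in the Abstract).** "Enrollment continued until September 2022, at which time the last group began the intervention". The same paragraph continues: "Data collection will be completed by December 2022, and data analysis will be completed by March 2023".
- **Schedule (Study Design).** "Interventions for both groups will last 4 months and will be comprised of 16 sessions". The assessments are "T0 (baseline), T1 (end of treatment), and T2 (follow-up at 6 months" after a starting point that this section does not name.
- **Anchor for T2 (Intervention).** After describing the questionnaire at the final meeting, the text says of the participants: "after 6 months, they will be contacted by the researchers for the follow-up assessment". This reads as 6 months after the end of the programme.
- **Missing data (Data Analysis).** "In the case of missing and unrecoverable data on the primary endpoints, we will assume that these events are related to chance". Then: "Analyses will be performed by applying list-wise deletion to remove cases with missing values from the final database in order to obtain unbiased estimates".

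**The concern.** The calendar and the assessment schedule cannot both be followed. If the calendar holds, the last group and other late starters never have the T2 that the design promises them, and the 6-month question is answered only on groups that started early. If the schedule holds, the published dates are wrong.

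The calendar reading also interacts with the missing-data rule. List-wise deletion drops a whole case when a value is missing. A repeated-measures ANOVA that includes T2 would therefore discard the T0 and T1 data of late starters as well. That loss is fixed by the start date, whereas the plan treats missing primary data as chance events. The 20% allowance in the sample size is for dropout, and nothing is reserved for a calendar cut-off.

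A cut by start date need not bias the arm comparison if groups in both arms started on similar dates, which the article does not state. The losses that do follow are in precision and in coverage of later cohorts.

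**Working it through.** **Inputs from the article.** Last start September 2022; programme 4 months, 16 sessions; T2 6 months after the final meeting (Intervention) or at 6 months with no stated origin (Study Design); data collection ends December 2022, taken as 31 December; analysis ends March 2023; 58 randomised, 48 required, dropout about 20%; groups of 3 to 12. **Not given:** session frequency, first start month within 2021, enrolment by date.

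**1. Last group, starts from 1 to 30 September 2022.** T1 = start + programme length; T2 = T1 + 6 months, or start + 6 months. Sixteen weekly meetings span 15 weeks from first to last.

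| Reading | T1 | T2 |
|---|---|---|
| Full 4 months, T2 after final meeting | 1–30 January 2023 | 1–30 July 2023 |
| Weekly sessions, T2 after final meeting | 15 December 2022 – 13 January 2023 | 15 June – 13 July 2023 |
| T2 from baseline | as above | 1–30 March 2023 |

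Every T2 date is after December 2022. The first two rows are also after the end of analysis; the third falls in the month when analysis is due to finish. With weekly sessions, starts up to 17 September (31 December minus 15 weeks) still reach T1 in time.

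**2. Latest start that reaches T2 by 31 December 2022.**
- 4 + 6 months: 28 February 2022.
- 15 weeks + 6 months: 17 March 2022.
- 6 months from baseline: 30 June 2022.

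**3. Share losing T2, assuming starts spread evenly by month up to September 2022.**
- T2 after a 4-month programme, so starts in March–September 2022 (7 months) lose it: 7/21 = 33% if the first start was January 2021; 7/15 = 47% if it was July 2021.
- T2 from baseline, so starts in July–September 2022 (3 months) lose it: 3/21 = 14%; 3/15 = 20%.

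A first start later than July 2021 would raise these shares. A one-third loss would leave 58 × 2/3 ≈ 39 before dropout, against 48 required.

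**4. What deletion could cost in power.** First, the plan's own figure. The article gives "obtained an average reduction in caregiver burden of 4.61 points, corresponding to an effect size of 0.243". Reading 0.243 as Cohen's f, with two groups, two times (m = 2), alpha .05 and an assumed correlation ρ = 0.5 (not stated), the noncentrality is λ = f²·N·m/(1 − ρ). For N = 48 this is 0.243² × 48 × 2/0.5 = 11.34, on 1 and 46 degrees of freedom, and power is 0.909. The smallest N with 90% power is 47, or 48 with equal arms, so 48 reproduces. The stated 58 is 48 × 1.2.

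With the same formula, and removing assumed numbers from 58 (one or two late groups of 3 to 12):

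| Removed | N | Power | N after 20% dropout | Power |
|---|---|---|---|---|
| 3 | 55 | 0.94 | 44 | 0.88 |
| 6 | 52 | 0.93 | 41 | 0.86 |
| 12 | 46 | 0.90 | 36 | 0.81 |
| 24 | 34 | 0.79 | 27 | 0.68 |

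For comparison, 20% dropout alone leaves 46 (58 × 0.8 = 46.4), with power 0.90. The table is an illustration, since the true number removed is unknown.

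**The case against.** The strongest reply is that December 2022 appears only in status paragraphs. The Methods contain no cut-off and plan T2 for both arms without exception, so a misstated forecast fits the text as well as a planned truncation does. This stands as a caution about intent: the article does not show that the investigators mean to cut follow-up short. It does not remove the conflict, because the sentence is unqualified and does not say that T2 is pending.

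Three stronger conclusions that a reader might draw are not supported:

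- **That the last group cannot have T1.** Session frequency is not stated. Weekly sessions from early to mid September could finish by late December, so T1 is borderline.
- **That the loss is far above the planned 20%.** The 33% and 47% figures need an even spread of starts and an assumed first month. Counting T2 from baseline gives 14–20%, which does not exceed 20%. With groups of 3 to 12, the 58 participants may sit in a few uneven cohorts.
- **That late cohorts will certainly be deleted.** No primary time point is named, and the sample size uses two times, baseline and follow-up. A T0–T1 analysis would keep everyone with T1. The missing-data text also concerns unrecoverable values, and an assessment not yet due is arguably not one. Deletion follows only if T2 is in the analysed data and the December date is enforced.

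**Conclusion.** The concern holds as an internal contradiction over T2. With a last start in September 2022, T2 falls in June–July 2023 after the final meeting, or in March 2023 from baseline, and data collection ends in December 2022 on either reading. This part rests only on stated dates and durations. On the schedule in the Intervention section it reaches beyond the last group, to any group started after about end of February to mid-March 2022.

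The size is uncertain. The number of participants affected cannot be derived. The range of 14–47% assumes even starts from January or July 2021 and varies with the T2 anchor. Removal by list-wise deletion is conditional on T2 being analysed. Even so, this is more than a clerical slip: followed as written, the plan forgoes follow-up that it has already scheduled.

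**What to change.** Reconcile the Results section and the Abstract with Study Design and Intervention:

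1. State the origin of the 6 months in Study Design, so that it agrees with Intervention.
2. Set the end of data collection at the last participant's T2: about July 2023 if counted from the final meeting, March 2023 if from baseline.
3. Move the final T2 analysis after that date in both places.
4. If December 2022 is kept, say that the analysis then covers T0–T1 for groups that have finished and that T2 is pending, so that assessments not yet due are not handled as missing under the list-wise rule.

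**Cost:** date changes in two places and a delay to the final T2 analysis. Data collection would end about 7 months later (December 2022 to July 2023), or 3 months later if T2 is from baseline. No assessments are added beyond those planned.

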## Discussion

Despite several available studies, there is still moderate evidence on the efficacy of psychosocial interventions for dementia caregivers. In fact, although understanding the needs of caregivers is essential for developing effective interventions, only a few systematically address them.

With this study, we expect to advance the state of the art in the field by evaluating the efficacy of a self-help intervention using an evidence-based approach. We will do this through an RCT study, aimed at improving caregivers’ quality of life, reducing their care burden, and easing their anxiety or depressive symptoms, which represent the most felt needs of the population of carers. Moreover, the study will also identify barriers and obstacles that may arise during the organization of group interventions, especially in the COVID-19 era, in which isolation and restriction in mobility may affect participation and relationship-building among the group.

The aim of this study is to analyze the impact of a psychosocial intervention dedicated to a group of informal caregivers of patients with Alzheimer disease; the intervention will be guided by a trained psychologist in order to facilitate the expression of the group members’ emotional states and will be compared to a traditional self-help group.

We focused on patients with Alzheimer disease because dementia is becoming one of the main conditions, worldwide, that causes a lack in self-sufficiency [25]. It is estimated that about 3 million people are directly or indirectly involved in the care and support of people with dementia. In particular, informal caregivers (ie, family members) [26,27] play a fundamental role in the lives of people with dementia because they provide both physical and psychological support to ill family members on a daily basis [28]. Therefore, it is important to provide support to the caregiver [29]. Our study compares two groups receiving different interventions: a self-help group and a psychosocial group with elements of emotional support.

The self-help group, based on its typical characteristics, is not a structured group and leaves the content to be decided by the participants. The experimental group is structured around topics defined by the facilitator or psychologist, focused on the experiences and needs of the caregivers, with particular attention paid to their personal emotional experience. We hypothesize that the experimental group will be more effective in managing caregiver burden and coping strategies, which could improve the perception of well-being, anxiety, and depression among caregivers. This is because since the experimental group is more structured, it provides more skills, advice, and support than the self-help group. This study may also give us more information about the most appropriate ways to support and help caregivers of people with dementia.

